## Abstract

This protocol presents a multilevel cluster randomized study in 24 communities in Cape Town, South Africa. The study comprises four specific aims. Aim 1, conducted during the formative phase, was to modify the original Couples Health CoOp (CHC) intervention to include antiretroviral therapy/pre-exposure prophylaxis (ART/PrEP), called the Couples Health CoOp Plus (CHC+), with review from our Community Collaborative Board and a Peer Advisory Board. Aim 1 has been completed for staging the trial. Aim 2 is to evaluate the impact of a stigma awareness and education workshop on community members’ attitudes and behaviors toward young women and men who use AODs and people in their community seeking HIV services (testing/ART/PrEP) and other health services in their local clinics. Aim 3 is to test the efficacy of the CHC+ to increase both partners’ PrEP/ART initiation and adherence (at 3 and 6 months) and to reduce alcohol and other drug use, sexual risk and gender-based violence, and to enhance positive gender norms and communication relative to HIV testing services (n = 480 couples). Aim 4 seeks to examine through mixed methods the interaction of the stigma awareness workshop and the CHC+ on increased PrEP and ART initiation, retention, and adherence among young women and their primary partners. Ongoing collaborations with community peer leaders and local outreach staff from these communities are essential for reaching the project’s aims. Additionally, a manualized field protocol with regular training, fidelity checks, and quality assurance are critical components of this multilevel community trial for successful ongoing data collection.

**Trial registration.** Clinicaltrials.gov Registration Number: NCT05310773. Pan African Trials: pactr.samrc.ac.za/ Registration Number: PACTR202205640398485.

## Introduction

South Africa continues to report high levels of alcohol consumption, increasing opiate use, and particularly high rates of methamphetamine and methaqualone use in certain areas [1–4]. Alcohol and other drug (AOD) use undermines women’s personal agency in negotiating condom use with their sexual partners and accessing healthcare services, posing barriers to ending the HIV epidemic [5–7]. The intersection of AOD use, sexual risk behavior, and gender-based violence (GBV) in South Africa creates a complex syndemic that increases HIV risk [7–9]. In South Africa, a historical backdrop of gender inequality within a patriarchal society has compounded women’s lack of sexual autonomy [10]. Continued heavy AOD use among young women and their partners exacerbates the risk of HIV transmission by contributing to outside sexual partnerships, GBV, impaired condom use, and reduced adherence to antiretroviral therapy (ART) [11]. HIV treatment as prevention, particularly ART and pre-exposure prophylaxis (PrEP) for protecting partners against HIV, has shown promising results in reducing HIV transmission [12]. However, successful implementation of ART and PrEP requires addressing relational and contextual factors and structural challenges [11].

The highest HIV incidence among women in South Africa occurs during young adulthood, often in the context of primary partnerships characterized by AOD use, condomless sex, and outside sexual partnerships [8,13]. Consequently, engaging male partners in the HIV continuum is crucial to support HIV prevention efforts [14,15]. While previous research has focused on age-disparate or intergenerational sexual relationships, there is a need to address the health and behaviors of primary male partners in tandem with young women [16,17].

Couples-based interventions have demonstrated efficacy in improving ART adherence and show promise in enhancing PrEP adherence [18,19]. By involving both partners, these interventions can effectively reduce HIV transmission [14,20,21]. For example, the original Couples Health CoOp (CHC), an empowerment-based intervention developed for young couples in South African, addressed AOD use, GBV, and sexual risk within relationships [22]. The CHC has shown positive outcomes for condom use, gender norms, and reducing HIV incidence among women [18,22]. Long-term outcomes included improved communication between couples [23]. However, the original CHC did not specifically address ART or PrEP uptake and adherence, highlighting the need for this modification.

Structural challenges also exist where young couples live. Stigma within communities has also been identified as a barrier to health services among people who use AODs or are living with HIV and for young women who are sexually active [24–26]. Adaptations of stigma and discrimination training directed by community members has been found to be effective [27–29].

This article presents the protocol for a cluster randomized trial aimed at evaluating the Couples Health CoOp Plus (CHC+) as a newly enhanced intervention that integrates ART/PrEP initiation and adherence with the existing CHC model and a structural intervention of stigma awareness workshops in communities. CHC+ incorporates added information on sexual and reproductive health, a status-neutral approach, treatment as prevention (U = U), and the significance of ART and PrEP.

To address structural factors, the study team developed a stigma reduction curriculum based on a stigma reduction toolkit and a community HIV prevention project [30] with community peers for a large community awareness with Stop and Go skits to tackle stigmatizing attitudes and behaviors toward young women and men who use AODs and who may need health services, including HIV treatment and prevention.

The research adopts a multilevel social ecological framework, emphasizing individual, couple, and structural factors in HIV risk and access to services [31,32]. The overarching goal is to implement a more comprehensive approach that addresses the intersecting epidemics of AOD use, sexual risk behavior, and HIV transmission among young couples in South Africa. By including ART/PrEP initiation and adherence, a stigma awareness workshop, in a multilevel approach, the study aims to enhance HIV prevention efforts, improve treatment outcomes, and alleviate the burden of HIV within this key population. The study findings hold the potential to guide future interventions and contribute significantly to helping end the HIV epidemic in South Africa.

### Study aims

This study comprises four specific aims. Aim 1, conducted during the formative phase, was to modify the original CHC intervention to include ART/PrEP with review from our Community Collaborative Board (CCB) and a Peer Advisory Board (PAB). Aim 2 is to evaluate the impact of a stigma awareness and education workshop on community members’ attitudes and behaviors toward young women and men who use AODs and other people seeking HIV services (testing/ART/PrEP) and other health services. Aim 3 is to test the efficacy of the CHC+ to increase both partners’ PrEP/ART initiation and adherence (at 3 and 6 months) and reduce AOD use, sexual risk and GBV, and enhance positive gender norms and communication relative to HTS. Lastly, Aim 4 seeks to examine through mixed methods the interaction of the stigma awareness workshop and the CHC+ on increased PrEP and ART initiation, retention, and adherence among young women and their primary partners (see **Fig 1** for SPIRIT schedule).

**Fig 1 pone.0305056.g001:**
[figure not shown]
Schedule of enrollment, interventions, and assessments.

#### Conceptual framework

**Fig 2** presents a comprehensive conceptual framework reflecting the multiple levels of the social ecological framework and the strategies to accomplish the aims for the individual, as a couple, and structural levels within their environment. The framework also incorporates the supports and challenges needed to address the multiple processes that will be used to accomplish the study aims.

**Fig 2 pone.0305056.g002:**
[figure not shown]
Social ecological framework and strategies.

## Materials and methods

The protocol for this study has been approved by the following health research ethics committees: South African Medical Research Council (primary institution: EC031-8/2020) and RTI International (defers to primary institution for approval).

### Setting and study design

#### Setting

City Health Clinics within or adjacent to historically disadvantaged communities in the Cape Town area that were selected for the government PrEP rollout were identified. After mapping these clinics, the clinics that were not accessible to potential participants due to distance were removed, resulting in a total of 24 clinic catchment areas or communities. The communities were classified by population groups, including Black, Coloured (of mixed ancestry—an official term used in South Africa for population classification), and some communities with both population groups.

#### Study research design

This study is a four-arm cluster randomized trial that has two interventions: a community stigma awareness workshop (for communities) and the CHC+ (for couples). Specifically, 24 Cape Town communities located near clinics that provide ART and PrEP were randomized into one of four arms (see **Fig 3**): (1) stigma awareness workshop (community) and HTS/PrEP/ART (couples); (2) stigma awareness workshop (community), and HTS/PrEP/ART with the CHC+ (couples); (3) no stigma awareness workshop (community) and HTS/PrEP/ART (couples; control); and (4) no stigma awareness workshop (community), and HTS/PrEP/ART with the CHC+ (couples). Twenty couples (a total of 480 couples), defined as young women and their primary male partners both aged 18 to 30 are recruited from each community. Depending on the study arm of their community, couples are provided with HTS/PrEP/ART and/or the CHC+. Couples are asked to return for two study follow-up appointments at 3- and 6-months post-enrollment. Communities are already assigned to receive either the stigma awareness workshop or no workshop, with baseline and repeated follow-up surveys with community members. Recruitment began in July 5, 2022 and is ongoing.

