#### Randomization

To achieve balance in allocation of population groups across the four study arms, stratified randomization by population group (Black African, Coloured, and Mixed) was conducted. A total of 24 catchment areas were selected from the list of 34 catchment areas. The sampling frame included 8 Black African, 8 Coloured and 8 Mixed communities. Within each of the 3 strata, the 8 areas were randomized to the four study arms in a 2:2:2:2 allocation.

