#### Implementation of the community stigma awareness workshop

After the brief baseline survey has been completed, community stigma awareness workshops will be conducted in communities that were randomly assigned to receive this stigma awareness activity (N = 12). We expect on average to reach 100 community members to attend these workshops. These workshops can occur within a week of survey completion. The workshops take place in various community settings, such as community library workrooms, churches, sports halls, or temporary tented areas within the community with a minimum of 50 attendees, meaning one or two workshops will be conducted per community. The workshops are facilitated by the field team leads, field staff, and PAB members. Extensive awareness campaigns are conducted within the communities to inform residents about the upcoming workshop, through marketing materials and advertising the workshop with music and a loudspeaker and by word of mouth. These workshops take approximately 2 to 3 hours. Following the workshop, participants can complete a voluntary exit survey that will assess participant satisfaction and elicit suggestions and recommendations on the workshop delivery. The workshop participants are also provided with ART and PrEP information leaflets and resource guides for local services such as substance use rehabilitation centers and mental health services.

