### Couples

#### Recruitment: Couples

To generate awareness among young people in the catchment areas surrounding the study clinics, trained outreach staff, comprising male-female pairs, will be strategically deployed. To ensure effective community engagement, the outreach staff will collaborate with the Peer Advisory Board (PAB), a group of young people with deep community connections and relevant lived experience. To minimize bias and protect the privacy and confidentiality of potential participants, PAB members will not be assigned to assist in their own communities. The outreach team will employ various methods, including mapping hotspots and establishing connections with local establishments, shops, salons, and community centers. Skilled and trained outreach staff who reflect the demographics and speak the languages of the study communities are trained in these methods. Recruitment materials, such as recruitment cards and flyers, will be strategically posted within the communities and shared on social media platforms frequently accessed by the target population. By utilizing a combination of in-person and virtual strategies, the outreach team aims to reach a wide range of potential participants and maximize recruitment efforts.

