#### Screening: Couples

During the initial contact, individuals will be approached, and verbal consent will be obtained to screen for eligibility. To ensure privacy and confidentiality, the screening process will be conducted individually, with female staff screening the female partner and male staff screening the male partner. In cases where both partners are not present during the initial outreach, screening appointments will be scheduled to facilitate simultaneous screening and determine preliminary eligibility. For the screening process, project staff will use a quick screener form, which allows for efficient and standardized assessment of eligibility criteria. To maintain the integrity of the screening process, staff members will compare answers away from the screened couple to determine initial eligibility. Individuals’ responses are not disclosed to their partner. To respect privacy, couples who are found to be ineligible are not be provided with explanations for their ineligibility, but they will be respectfully informed that they do not meet the criteria for participation. After this initial eligibility screening, biological verification for eligibility is scheduled and conducted at the project site. Both partners are tested for HIV and the female partner is tested for pregnancy. If either partner has an indeterminant HIV test or the female partner has a positive pregnancy test, they are both not eligible.

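### Couples are enrolled after their community's arm is fixed, with no stated step keeping CHC+ status from them until baseline, so differential enrolment is possible and the planned adjustment would not reliably capture it

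*Protocol article*

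**What the plan says.** **Allocation.** Under Study research design, "24 Cape Town communities located near clinics that provide ART and PrEP were randomized into one of four arms". Under Randomization, "Within each of the 3 strata, the 8 areas were randomized to the four study arms in a 2:2:2:2 allocation", which gives six communities per arm. Couples are not randomised individually: "Depending on the study arm of their community, couples are provided with HTS/PrEP/ART and/or the CHC" (the plus sign of CHC+ follows). On timing, "Recruitment began in July 5, 2022 and is ongoing", so couples were still being enrolled after the communities had been allocated.

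**Finding couples.** Recruitment: Couples describes mapping of hotspots, links with local shops and salons, cards, flyers and social media, and says that "the outreach staff will collaborate with the Peer Advisory Board (PAB), a group of young people with deep community connections". The one measure described there as limiting bias is that PAB members do not help in their own communities. The target is 20 couples per community.

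**Entry criteria.** Participant eligibility: Couples relies on reports of weekly AOD use, condomless sex, an outside partner, intention to stay together and no recent PrEP/ART use. Partners are screened separately with a standard form, and "staff members will compare answers away from the screened couple to determine initial eligibility". HIV and pregnancy tests follow at the project site. Consent comes next, and the ACASI questionnaire and urine drug screen belong to the baseline assessment.

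**Adjustment.** The Statistical analysis plan and hypotheses section adds covariates if demographics or clinic characteristics differ significantly across arms. It also looks at associations with mediators and moderators to decide which variables enter the models.

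**The concern.** Randomising communities protects the comparison only if the couples who enter do not depend on the arm. Here each community has a single arm, fixed before its couples are sought. If a couple hears before consent that joint sessions are or are not on offer, the decision to take part can depend on the arm. A couple willing to attend two joint sessions may be more cohesive or readier to start treatment than a couple willing to accept HTS/PrEP/ART alone.

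Readiness and cohesion are plausible predictors of the primary outcomes, ART/PrEP initiation and adherence. If CHC+ communities enrolled more such couples, part of any difference would be selection and not effect. Stratifying by population group does not address this. GEE clustering does not either, because it corrects the variance and leaves the bias in the estimate.

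**Working it through.** **1. Design structure.** 24 communities x 20 couples = 480; 4 arms x 120 = 480. Both agree with the stated total. CHC+ against HTS compares 12 with 12 communities (240 couples each side). A contrast of two single arms compares 6 with 6 (120 each side).

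**2. Sequence.** The article's order is: community allocated; couple approached; screened; HIV and pregnancy tested; consented; baseline ACASI. No section says when couples learn whether their community receives CHC+.

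**3. What the adjustment can see.** The trigger is a significant difference in demographics or clinic characteristics. Treatment readiness is neither. It is named under Overall study measures as part of the RRBA. The baseline section lists relationship dynamics among its domains but does not name readiness.

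**4. Size, as an illustration.**
- From the article: 20 couples per community, ICC 0.05, two-sided 5% test.
- Assumed, because the article gives no initiation or consent rates: ready couples initiate at 45%, others at 20%; overall initiation 30%; ready share 10, 20 or 30 points higher in CHC+ communities; no true effect.

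Bias = difference in ready share x (0.45 - 0.20):
- 0.10 x 0.25 = 2.5 points
- 0.20 x 0.25 = 5.0 points
- 0.30 x 0.25 = 7.5 points

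Design effect = 1 + (20 - 1) x 0.05 = 1.95.

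SE = sqrt(2 x p(1 - p) x 1.95 / n), with p = 0.30:
- n = 240: sqrt(2 x 0.21 x 1.95 / 240) = 0.0584
- n = 120: sqrt(2 x 0.21 x 1.95 / 120) = 0.0826

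The rejection probability comes from the non-central t with non-centrality bias/SE, on 22 df (12 versus 12) or 10 df (6 versus 6):

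| Bias | 12 vs 12 | 6 vs 6 |
|---|---|---|
| 2.5 points | 6.9% | 5.9% |
| 5.0 points | 13.0% | 8.5% |
| 7.5 points | 23.3% | 13.1% |

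**5. Sensitivity.** With a 5-point bias and 12 versus 12 communities, the rate is 15.5% at p = 0.20 and 11.7% at p = 0.50. With a 1-point bias at p = 0.30 it is 5.3%, which is practically nominal.

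**The case against.** The strongest reply is that this argues from silence in a condensed article. Recruitment scripts, consent wording and the timing of disclosure normally sit in field manuals, and the article refers to manualised procedures that are not shown. That stands as a limit: the article does not show that CHC+ status is disclosed early. It is why the fix asks first for a statement if concealment already exists. It does not remove the point, because enrolment after allocation is the stated design and the adjustment rule is stated too.

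A reader might infer that every couple's allocation is known before enrolment. The documents do not support that. The sentence "Communities are already assigned to receive either the stigma awareness workshop or no workshop" concerns only the stigma workshop. That workshop is publicly advertised, but no section says that recruiters, screeners or couples know CHC+ status.

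A reader might also infer that the workshop team screens couples and takes consent. It is true that "The workshops are facilitated by the field team leads, field staff, and PAB members", and that PAB members support couple outreach. But screening is given to project staff and consent to study staff, and the article does not say that these are the same people. That sentence also concerns the stigma workshop. CHC+ is delivered by trained project staff. Changing the recruitment rota would therefore not address selection on CHC+.

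There are real safeguards: common criteria, separate screening with a standard form, two biological tests, the same target in each community, and HTS/PrEP/ART in all arms. CHC+ adds only about two hours over two sessions. These narrow the scope for selection, but none of them addresses a couple's decision to take part.

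Finally, the covariate step could admit readiness as a mediator or moderator. It could, but the article does not commit to it.

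**Conclusion.** The concern holds as a design risk, not as a demonstrated bias. Couples enter by discretionary outreach and largely on self-report after their community's arm is fixed, and no stated step keeps CHC+ status from them until baseline is complete. The adjustment rule would not reliably capture a difference in readiness or relationship.

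The false-positive figures of about 7% to 23% for a bias of 2.5 to 7.5 points (12 versus 12 communities) rest on assumed initiation rates and assumed gaps in the ready share. The documents support neither those gaps nor a direction of bias, and a small gap would leave the test close to nominal. The point merits a change because the remedy is cheap, not because the damage is established.

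**What to change.** 1. **Recruitment and consent.** For couples still to be enrolled, use the same arm-neutral recruitment and consent wording in all 24 communities, saying that couple workshops may or may not be offered. Tell couples their community's CHC+ status only after both partners have consented and completed the baseline ACASI. If this is already practice, state it in Recruitment: Couples and Informed consent: Couples.
2. **Reporting.** Report the numbers of couples approached, screened, eligible and consented by arm.
3. **Analysis.** In Statistical analysis plan and hypotheses, prespecify a sensitivity analysis of ART/PrEP initiation and adherence adjusted for baseline treatment readiness and relationship measures from the RRBA. Run it whatever the baseline significance tests show, provided these measures are collected at baseline.

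**Cost.** An ethics amendment for the wording, an enrolment log where none exists, and one further analysis; no extra visits or participants. Concealment from couples will be imperfect once earlier CHC+ couples have talked. Only couples not yet enrolled benefit from the procedural change. For those already enrolled, the counts (where recorded) and the adjusted analysis can reveal or reduce a difference but cannot prevent it.

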**Fig 3 pone.0305056.g003:**
[figure not shown]
Multilevel research design.

#### Randomization

To achieve balance in allocation of population groups across the four study arms, stratified randomization by population group (Black African, Coloured, and Mixed) was conducted. A total of 24 catchment areas were selected from the list of 34 catchment areas. The sampling frame included 8 Black African, 8 Coloured and 8 Mixed communities. Within each of the 3 strata, the 8 areas were randomized to the four study arms in a 2:2:2:2 allocation.

